## Abstract

**Background:**

Residents living in nursing homes usually have complex healthcare needs and require a comprehensive care approach to identifying and meeting their care needs. Suboptimal quality of care is reported in nursing homes and is associated with the poor health and well-being of the residents, the burden on acute care hospitals and the high costs of healthcare for the government.

The aim of this study is to test the hypothesis that an Aged Care Clinical Mentoring Model will create and sustain evidence-based quality improvement in priority areas and will be cost-effective in nursing homes in Hunan Province, China.

**Methods:**

A cluster randomized controlled trial will be applied to the study. Fourteen nursing homes will be randomly allocated to either the intervention group (*n* = 7) or the control group (*n* = 7). Forty staff will be recruited from each nursing home and the estimated sample size will be 280 staff in each group. The intervention includes a structured, evidence-based quality improvement education program for staff to facilitate knowledge translation in evidence-based quality improvement targeting urinary incontinence, pressure injury and falls prevention. The primary outcomes are nursing homes’ capacity to create and sustain quality improvement, staff perceptions of person-centered care, self-reported quality of care by residents and selected quality indicators at 12 months follow-up adjusted for baseline value. Secondary outcomes are residents’ quality of life, residents’ unplanned admissions to acute care hospitals, quality of care reported by staff, staff job satisfaction and staff intention to leave adjusted for baseline value. A mixed linear regression model will be adopted to compare the significant differences between groups over a 12-month period.

**Discussion:**

Although the Aged Care Clinical Mentoring Model has been tested as an effective model to bring positive changes in nursing homes in a high-income country, factors affecting the adaptation of the model in nursing homes in low- and middle-income countries are unknown. The carefully planned intervention protocol enables the project team to consider enablers and barriers when adapting the Model. Therefore, strategies and resources will be in place to manage challenges while demonstrating best practice in this study.

**Trial registration:**

Prospectively registered via Chinese Clinical Trial Registry (ChiCTR), ChiCTR-IOC-17013109, Registered on 25 October 2017.

**Electronic supplementary material:**

The online version of this article (10.1186/s12913-018-3596-6) contains supplementary material, which is available to authorized users.

## Background

The Chinese population is aging dramatically due to improved life-expectancy and a decrease in fertility rate [1]. In 2016, the number of people aged over 60 years reached 230 million [2]. It was also estimated that more than 100 million people aged 60 years or over had chronic diseases [3]. The number of older people living with disabilities reached 37 million and those living with dementia reached 9.19 million [3]. The demand for nursing home care for older people with high-dependence care needs has reached an unprecedented high in China [1]. By 2016, the number of nursing homes was 140 thousand with 7.3 million beds, and the average annual growth rate of nursing home beds was 8.6% nation-wide [4]. The majority of residents in nursing homes have dementia or cognitive impairment [5]. The rapid growth of nursing homes has raised great concern in the public about the quality of care for nursing home residents in China [6]. There are few evidence-based intervention studies to improve quality of care in nursing homes. This study will address the gap in research by adapting and evaluating an Aged Care Clinical Mentoring Model that has been tested as an effective model of change in evidence-based quality improvement in nursing homes in Australia [7].

Similar to many low- and middle-income countries, China has experienced significant social and economic transitions in the past four decades, characterized by improved employment rates for women and increased internal migration for employment or career development opportunities. This surge in employment for women has weakened the traditional family-based care for older people, [1] the demand for nursing home care for older people has increased dramatically due to the lack of family caregivers [1, 8]. However, nursing homes are currently underdeveloped to provide residents with high-quality care, evidenced by reports on unmet care needs, suboptimal care and high hospitalization rates [6].

Lack of workforce development to implement evidence-based quality of care for residents is one of the key factors amongst many that contribute to undesirable care outcomes in nursing homes [9]. Registered nurses are a minority in the workforce in nursing homes, and have limited educational preparation in leading nursing home care [10]. A large proportion of staff members in nursing homes are untrained personal care assistants (PCAs) who are mainly migrant workers from rural areas and have low levels of education with little to no training in nursing home care [10]. In addition, a low staff to resident ratio in nursing homes is widely reported and is attributed to unmet care needs for residents [10].

Quality of care is defined as “the degree to which health services for individuals and populations increase the likelihood of desired health outcomes and are consistent with current professional knowledge” [11, 12]. This definition strongly suggests that quality improvement needs to be based on current research evidence. Staff education about evidence-based practice and knowledge translation activities are two crucial components in evidence-based quality improvement [7, 13]. However, nursing homes are usually perceived as resource-poor settings for implementing evidence-based quality improvement [14]. Building nursing homes’ capacity to create and sustain quality improvement is a priority in the aged care system to ensure that quality of care is achieved [15].

The most frequently reported indicators of poor quality care in a Chinese nursing home context are falls, fall-related injuries, pressure ulcers and urinary incontinence among residents. Residents living with dementia are associated with a high risk of these poor quality care outcomes [16]. The estimated prevalence rate of urinary incontinence is around 65.8%, the fall rate is around 14.7–34% and the pressure ulcer rate is around 7.1–25% in nursing homes in China [17–19]. Prevention of these adverse events has been identified as a priority quality improvement as they have negative consequences for residents and for healthcare costs [18].

Clinical Mentor as a model of change in evidence-based quality improvements has been widely reported and recognized as a successful model globally [20, 21]. An Aged Care Clinical Mentor (ACCM) is defined as “a leader who facilitates improved quality of care for older people using best practice by providing and encouraging professional development in colleagues through communication, education and peer support” [9, 21, 22]. In the ACCM model in Australia, Registered Nurses (RNs) were prepared and supported to lead evidence-based quality improvement activities and were appointed as a clinical mentor for care staff (mentees). The ACCM model was initiated by the Australian Government and was tested in four aged care facilities and four community aged care settings across two states in Australia [9, 22]. The results revealed that the ACCM model was an effective workforce model to improve aged care organizations’ capacity to create and sustain quality improvement [9]. The aim of this study is to create and sustain quality improvement in nursing homes by implementing the ACCM model in Hunan Province, China.

## Methods

### Study design

The ACCM model will be tested using a single-blind cluster randomized controlled trial (RCT) design. The study will be undertaken in Hunan Province, the seventh largest populated province in China, and home to 12.01 million people aged 60 or over where one-sixth of them were living with disabilities in 2015 [23]. Fourteen nursing homes in Hunan Province will be randomly selected and divided into two groups: the intervention group and the control group. Cluster RCT will be applied to the study to reduce influence from the interplay of subjects from the same nursing home. Because of the nature of the intervention, it is not possible to mask the study assignment from the research interventionists (the project team who will deliver the intervention), though staff at participating sites will be unaware of group assignment. The outcomes assessment will be performed by independent investigators who will be blinded to the group assignment. The standard protocol items named “Recommendations for Interventional Trials (SPIRIT)” that provides an overview of schedule of enrolment, interventions and assessments is presented in Table 1. The SPIRIT checklist is shown in Additional file 1.

**Table 1 Tab1:**
[figure not shown]
schedule of enrolment, interventions and assessments

### Hypotheses

Primary hypothesis: Nursing homes that implement the ACCM model will report enhanced capacity to create and sustain evidence-based quality (H_1_), improved staff perceptions of person-centered care (H_2_), and higher levels of residents’ or their families’ perception of quality of care (H_3_) compared to the control group.

Secondary hypothesis: Nursing homes that implement the ACCM model will report improved quality of life for residents (H_4_), reduced unplanned admissions to acute care hospitals (H_5_), higher staff perception of quality of care (H_6_), increased job satisfaction for staff (H_7_), and decreased staff intention to leave (H_8_).

### Inclusion and exclusion criteria

Nursing homes will be included in the study if: (i) they have 150 beds or more; (ii) they have RNs in each unit; (iii) they are willing to participate in the study voluntarily. Nursing homes will be excluded from the study if they are participating in other training and research activities.

### Participants and sample size

Participants will be staff who provide direct care for residents. The sample size is based on one of the primary outcomes: staff perceptions of person-centered care measured by the ‘Approaches to Dementia Questionnaire’ (ADQ). In an earlier cluster RCT to improve care quality and safety through a 12-month clinical leadership program in aged care [24], the researchers found no differences in care staff attitudes toward dementia and dementia care assessed by ADQ between the intervention and control sites at 12 months post-intervention. Therefore, in our study, we have set a clinically meaningful change of 1.0 ADQ scores and 85% power to detect a difference of 1.2 standard deviation between groups at the 5% level of significance.

Since randomization will be conducted by the nursing homes (clusters), the sample size was adjusted to take into account the design effect. We have considered a large intra-class correlation coefficient of 0.26 (average estimate from a nursing home staff training intervention carried out in England and Wales [25]) and an average cluster size of 40 nursing staff. Assuming an alpha error of 0.05 and a beta error of 20%, the required cluster number was 7 for each group (251 nursing staff per group). Allowing for an attrition rate of 10–12%, we would require around 280 staff in each arm of the project.

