### Outcome measures and data collection

#### Primary outcomes

Primary outcomes include: (i) Nursing homes’ capacity to create and sustain quality improvement; (ii) Staff perceptions of Person-centered Care; (iii) Self-reported quality of care by residents; and (iv) quality indicators that include falls, fall-related injuries, pressure ulcers and urinary incontinence at 12 months follow-up adjusted for baseline value.

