#### Instruments

The instruments and their relationship to outcomes and hypotheses are presented in Table 3 [12, 27–33].

**Table 3 Tab3:** Description of instruments used in outcome measures

Outcomes	Instruments description	Hypotheses
Nursing homes’ capacity to create and sustain quality improvement	Shortell’s Organization and Management Survey had been adapted to nursing home to evaluate nursing homes’ capacity to create and sustain quality improvement by Scott [27]. The scale has 35 items, consists of 5 subscales related to communication and leadership. Cronbach’s α of the Chinese version is 0.87 [27].	H_1_- nursing homes’ capacity to create and sustain evidence-based quality
Perceptions of quality of care	A single item on a 4-point Likert scale which is dichotomized as very low or rather low opposed to rather high or very high [12].	H_6_&H_3_ - perception of quality of care
Person-centered Care Assessment Tool	Person-centered Care Assessment Tool consists of three subscales: the extent of personalizing care, amount of organizational support, degree of environmental accessibility, Cronbach’s α of the Chinese version is 0.68 [28, 29].	H_2_- staff’s perceptions of Person-centered Care
Staff job satisfaction	Minnesota Satisfaction Questionnaire in short form has 20 items was used to examine satisfaction with professional life, Cronbach’s α of the Chinese version is 0.95 [30].	H_7_- job satisfaction
Staff intentions to leave	Turnover Intention Scale has 6 items and Items are scored using 4-point Likert. The Chinese version has been tested and used to assess the turnover intention of care staff. Cronbach’s α of the Chinese version is 0.92 [31].	H_8_- staff intention to leave
Residents’ quality of life	The12-item Short-Form Health Survey has 8 domains include Physical Functioning, Role-Physical, Bodily Pain, General Health, Vitality, Social Functioning, Role-Emotional, and Mental Health. Cronbach’s α of the Chinese version is 0.91 [32].	H_4_- residents’ quality of life
	Quality of Life in Late-Stage of Dementia has 3 factors and 11 items, with the factors being depressive mood, behavioral symptoms of discomfort, and positive behavioral signs of social interaction. Cronbach’s α of the Chinese version is 0.74 [33].	

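### The sample size is calculated on the ADQ, but Table 3 measures the same primary outcome (H2) with a different instrument, so the stated power applies to no instrument listed there

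*Protocol article*

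**What the plan says.** Under Participants and sample size, the protocol article states "The sample size is based on one of the primary outcomes: staff perceptions of person-centered care measured by the" ADQ. It refers to an earlier cluster trial in which "the researchers found no differences in care staff attitudes toward dementia and dementia care assessed by ADQ". The target difference is then fixed on that scale: "we have set a clinically meaningful change of 1.0 ADQ scores". The power statement attached to this target is worded as "85% power to detect a difference of 1.2 standard deviation between groups at the 5% level of significance". The next paragraph gives an ICC of 0.26, 40 staff per home, alpha 0.05 and a beta error of 20%. From these it derives 7 homes and 251 staff per arm, or around 280 after attrition.

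Under Instruments, the article says "The instruments and their relationship to outcomes and hypotheses are presented in Table 3". The row of Table 3 for H2, staff perceptions of person-centered care, reads "Person-centered Care Assessment Tool consists of three subscales: the extent of personalizing care, amount of organizational support, degree of environmental accessibility" and gives a Cronbach's alpha of 0.68. The ADQ has no row in Table 3.

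The primary outcome list names the construct without an instrument. The sections on data collection and statistical methods do not mention the ADQ. Outside the sample-size section it appears only in the list of abbreviations.

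**The concern.** One primary outcome has two different instruments in two sections, and the only sample-size calculation uses the one missing from the instrument table. They do not look like two names for one scale. The article describes the ADQ result of the earlier trial as staff attitudes toward dementia and its care, whereas the Table 3 tool covers personalization of care, organizational support and environmental accessibility.

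Two things are at stake. First, if the Table 3 tool is analysed, the plan says nothing about the difference the trial was built to detect on it, since a 1.0-point difference on the ADQ has no stated equivalent there. Second, if both scales are collected, nothing says which governs H2, and the choice could be made after the data are seen. Because the model adjusts for the baseline value, the instrument has to be fixed before the first survey: a baseline that was not collected cannot be recovered.

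**Working it through.** **Inputs from the article.** Difference 1.0 ADQ point; the figure 1.2, whose wording is unclear; ICC 0.26; 40 staff per home; 7 homes per arm; two-sided 5%; beta 20%; attrition 10–12%.

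**Step 1. Reproduce the stated size.** The design effect is 1 + (40 − 1) × 0.26 = 11.14. The size per arm before clustering is 2 × [SD × (z₀.₉₇₅ + z₁₋β) / difference]².

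| Reading of 1.2 | Power | Per arm after design effect | Homes per arm (÷ 40) |
|---|---|---|---|
| SD of 1.2 points, difference 1.0 | 80% | 22.605 × 11.14 = 251.8 | 6.3, so 7 |
| SD of 1.2 points, difference 1.0 | 85% | 25.858 × 11.14 = 288.1 | 7.2, so 8 |
| Standardised difference of 1.2 | 80% | 121.4 | 3.04 |
| Standardised difference of 1.2 | 85% | 138.9 | 3.5 |

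Only the first row gives the stated 251 and 7 homes. With 10% attrition, 251 / 0.9 = 279, which is the stated figure of around 280. So the calculation uses an SD of 1.2 ADQ points, an effect of 1.0 / 1.2 = 0.83 SD, and 80% power. Reading 1.2 as an SD in points is an interpretation, chosen because it alone reproduces the result.

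**Step 2. Look for the same inputs on the Table 3 tool.**

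| Input | ADQ (sample-size section) | Person-centered Care Assessment Tool (Table 3) |
|---|---|---|
| Meaningful difference | 1.0 point | not given |
| SD | 1.2 (as read above) | not given |
| ICC | 0.26, from a staff training study; instrument not named | not given |
| Row in Table 3 | none | H2 |

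No required sample size or power can be computed for the listed tool from the article.

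**Step 3. What 7 homes per arm can detect on any scale, in SD units.** Take 36 completers per home (251 / 7 = 35.9) and assume that the ICC of 0.26 carries over.

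- Variance of a home mean: 0.26 + 0.74 / 36 = 0.2806.
- Standard error of the arm difference: √(2 × 0.2806 / 7) = 0.283 SD.
- Minimum detectable effect at 80% power, normal approximation: (1.960 + 0.842) × 0.283 = 0.79 SD.
- The same with t on 12 df (14 homes − 2), where the noncentrality needed is 3.053: 3.053 × 0.283 = 0.86 SD.

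Over an assumed ICC of 0.05 to 0.40, the range is 0.41 to 0.97 SD (normal) or 0.45 to 1.05 SD (t on 12 df). These figures describe precision. They say nothing about which difference would matter.

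**The case against.** The strongest reply is that the ADQ may simply be the intended H2 scale. The sample-size section says the outcome is measured by it, the abbreviation is kept, and the schedule of assessments in Table 1 might list it. The error would then be a missing row in Table 3, and the calculation would stand as written. This is a fair possibility and cannot be excluded. It does not remove the conflict, because Table 3 would still name a different instrument for H2.

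A reader might infer three stronger things that the documents do not support.

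- **That the ADQ is not collected.** Its absence from Table 3 suggests this, but the content of Table 1 was not available, so it is not shown.
- **That the calculation supports no planned analysis.** The sized construct is a planned primary outcome. The calculation depends only on the 0.83 SD ratio and the ICC, and would carry over if both were justified for the Assessment Tool. What is missing is that justification.
- **That power on the Assessment Tool is low.** Any such figure needs an SD that the article does not give and would apply an ADQ point to another scale. At 0.83 SD, power is 84% by normal approximation and 77% with t on 12 df. That gap comes from the few homes, not from the instrument mismatch. Baseline adjustment could close it: if baseline explained an assumed 10% or 25% of the variance of home means, the 77% would become 81% or 88%.

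It is also true that what a null result excludes is read from the confidence interval, not from the planned power. The mismatch therefore does not make a null result uninterpretable. It leaves no stated meaningful difference on the listed tool against which to judge the interval.

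**Conclusion.** The contradiction stands: the sample-size section and Table 3 name different instruments for H2. The stated 251 per arm and its power rest on the ADQ and attach to no instrument in Table 3. The arithmetic is not at fault, since it reproduces at 80% power with the 1.2 read as an SD in points.

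The effect on power for the listed tool cannot be quantified from the article. The most that can be said is that 7 homes per arm detect about 0.86 SD (t on 12 df) or 0.79 SD (normal) at 80% power. This assumes 36 completers per home, an ICC of 0.26 and no gain from baseline adjustment. Confidence is high for the mismatch and does not extend to any claim that the trial is underpowered.

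**What to change.** Name one instrument for H2, in every section, before baseline data are collected. There are two ways to do it.

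1. **Keep the ADQ.** Add it to Table 3 as the H2 measure and include it in all three surveys (before the intervention, 6 months, 12 months). The calculation then stands on its own scale. State the 1.2 explicitly as an SD in points if that is what is meant. The cost is a wording change and, if the ADQ is not already scheduled, one more questionnaire per wave.
2. **Keep the Person-centered Care Assessment Tool.** Rewrite the sample-size section with a justified meaningful difference, SD and ICC for that tool, and report the power that 7 homes per arm gives for it. Also state the minimum detectable effect (about 0.86 SD with t on 12 df, or 0.79 SD by normal approximation, under the assumptions above) as a precision figure. It should not become the target, because that would define the meaningful difference as whatever 7 homes can detect. Update it with the SD and ICC from pooled, arm-blind baseline data. The cost is wording and one recalculation. If the result shows that 7 homes per arm give too little power for the justified difference, the article should say so plainly.

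If both scales are kept, label one as the primary H2 measure and the other as supportive.

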### Statistical methods

Data from the trial will be analyzed using STATA software version 14.0 (Stata Corp, College Station, Texas, USA). All data will be checked for accuracy and a missing data analysis will be undertaken. The trial will adhere to the ‘CONSORT statement: extension to cluster randomized trials’ [34]. The data will be analyzed on an intention-to-treat basis, based on patient assignment.

A mixed linear regression model will be adopted to compare the significant differences between groups over a 12-month period. The mixed linear regression model will be adjusted by baseline value and potential confounding variables, for example, the sites and staff education levels [35]. Two-sided tests will be performed for all analyses and the level of significance will be set at *P* < 0.05. Where appropriate, 95% confidence interval will also be reported along with the *P* values.

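### The sample-size paragraphs give two powers (85% and 80%) and word the effect as 1.2 SD, but 251 staff per group follows from 0.83 SD at 80% power

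*Protocol article*

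**What the plan says.** All the sample-size inputs are in the protocol article under Participants and sample size. The outcome is the Approaches to Dementia Questionnaire (ADQ) score.

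- First paragraph: "we have set a clinically meaningful change of 1.0 ADQ scores and 85% power to detect a difference of 1.2 standard deviation between groups", with a 5% significance level.
- Second paragraph: an ICC of 0.26, an average of 40 staff per home, and then "Assuming an alpha error of 0.05 and a beta error of 20%, the required cluster number was 7 for each group (251 nursing staff" in each arm). With 10–12% attrition, this becomes about 280 staff per arm.

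Under Statistical methods, "Two-sided tests will be performed for all analyses and the level of significance will be set at" 0.05. The same section plans a mixed linear model adjusted for the baseline value and possible confounders. No baseline correlation is given, and the article does not say whether the sample-size formula used a normal or a t reference.

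**The concern.** Two things conflict on the face of the text.

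1. **Power.** The target is 85%, but the derivation uses "a beta error of 20%, the required cluster number was 7 for each group". These are two powers for one outcome and one sample size.
2. **Effect.** The first paragraph names a meaningful change of 1.0 point and then a power target "to detect a difference of 1.2 standard deviation between groups". Read as written, the trial is sized for a difference of 1.2 SD. That is 1.2/0.833 = 1.44 times the standardised effect that a 1.0-point difference with an SD of 1.2 points would represent.

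This is the only justification of sample size in the article. If the result is null, readers will use it to judge which effects the trial could have detected, and the printed text gives them incompatible answers.

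**Working it through.** **Inputs from the article:** two-sided alpha 0.05; power 80% or 85%; ICC 0.26; 40 staff per home; 7 homes per arm; the figures 1.0 and 1.2.

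**Formulas (normal approximation)**

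- Design effect: DE = 1 + (40 − 1) × 0.26 = 11.14.
- Staff per group: n = 2 × (z₀.₉₇₅ + z_power)² / d² × DE, with z₀.₉₇₅ = 1.960, z₀.₈₀ = 0.8416, z₀.₈₅ = 1.0364.

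**Step 1. Reproduce the plan's 251.** Take 1.0 as the difference in points and 1.2 as the SD in points, so d = 1.0/1.2 = 0.833. At 80% power, n = 2 × (2.8016)² / 0.833² = 22.60, and 22.60 × 11.14 = 251.8. This matches 251. Dividing by 40 gives 6.3 homes, rounded up to 7. Attrition: 251/0.90 = 279 and 251/0.88 = 285, consistent with about 280.

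**Step 2. Try the other readings of the text.**

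| Standardised effect | Power | n before DE | n per group | Homes per arm |
|---|---|---|---|---|
| 0.83 SD | 80% | 22.60 | 251.8 | 6.3 → 7 |
| 0.83 SD | 85% | 25.86 | 288.1 | 7.2 → 8 |
| 1.2 SD | 80% | 10.90 | 121.4 | 3.0 → 4 |
| 1.2 SD | 85% | 12.47 | 138.9 | 3.5 → 4 |

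Only the first row gives 251. One-sided versions of these rows do not match either: at 0.83 SD they give 198 (80%) and 231 (85%).

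**Step 3. Power of 7 homes per arm at 0.83 SD, normal formula.**

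- With 40 analysed staff per home, the standard error in SD units is √(2 × 11.14/280) = 0.282. The ratio is 0.833/0.282 = 2.954, and power is Φ(2.954 − 1.960) = 84.0%.
- With 36 per home, DE = 10.10 and power is 83.7%.
- With exactly 251 per group and DE 11.14, power is 79.9%.

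So 80% is met, and rounding up to whole homes adds about 4 points. The 85% is narrowly missed.

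**Step 4. Small number of homes.** With 14 randomised homes, an unadjusted between-home comparison has 2 × 7 − 2 = 12 df. Noncentral t, critical value 2.179:

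| Staff analysed per home | Power at 0.83 SD | Difference for 80% | Difference for 85% |
|---|---|---|---|
| 40 | 77.4% | 0.86 SD | 0.92 SD |
| 36 | 77.1% | 0.86 SD | 0.92 SD |

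On the same basis, 8 homes per arm with 40 staff each would give 83.5% and 9 would give 88.2%.

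**Step 5. The printed 1.2 SD taken literally.** With 7 homes per arm, power for 1.2 SD is about 97% (t, 12 df) or 99% (normal).

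**The case against.** The strongest reply is that the sample size itself is sound and only the wording is loose. Much of this stands. The 251 and the 7 homes reproduce, about 280 follows at 10% attrition, and the 80% is correct by the standard design-effect formula.

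A reader might infer that the stated power is simply wrong because 14 homes deliver only 77%. The documents do not support that. The 77% is an unadjusted t calculation on 12 df with equal home sizes, whereas Statistical methods plans baseline adjustment. If adjustment reduces the variance by a factor 1 − r² (an assumption), a correlation of about 0.27 would restore 80% on 12 df with 36 staff per home, and about 0.43 would restore 85%. No correlation is stated, so the gain is unknown, but so is a shortfall. In the other direction, unequal home sizes would lower the figure, as would losing df to the four ownership-and-size categories (about 75% if 9 df remained, also an assumption). The choice of reference distribution is a detail that an article may leave to a fuller document.

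A reader might also infer that the text as written overstates power, or that more staff in the same homes could never lift power above 80%. Neither holds in general. Read literally, 85% for a 1.2 SD difference understates power (about 97%). The ceiling of 80% with unlimited staff per home belongs to the unadjusted t calculation only; the normal formula's limit is 86%.

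What the reply does not remove is the contradiction. No other document can make 85% and 80% the same power, or make a 1.2 SD difference generate 251.

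**Conclusion.** The point holds as an internal contradiction in figures that readers will rely on. The effect behind the sample size is very probably 0.83 SD at 80% power, with the SD of 1.2 points misworded as the difference to detect. That is an inference from the arithmetic, and only the sponsor can confirm it.

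Under that reading, the 85% fails for the effect that generated the sample: it needs 288 analysed staff per group against 280 recruited before attrition, and 7 homes per arm reach at most 84% even by the favourable normal formula. The 80% stands on that formula. The t-based figure of about 77% is a caution about having only 14 homes, some 3 points below 80%, and is conditional on no gain from baseline adjustment.

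**What to change.** The sponsor should confirm the difference, the SD and the power that were used, and restate the two paragraphs as one consistent set.

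If the inputs are those that reproduce 251, the text should give a 1.0-point ADQ difference, an SD of 1.2 points (0.83 SD), two-sided 5%, ICC 0.26, 40 staff per home and 80% power by normal approximation. Both the 85% power and the description of the effect as a 1.2 SD difference should then be removed.

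The text should add that, with 7 homes per arm, an unadjusted t-based calculation on 12 df gives about 77% power for 0.83 SD, or 80% power for 0.86 SD. Any gain claimed from baseline adjustment should come with the assumed correlation.

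The cost is a rewrite of one short section and a slightly less favourable stated power. No extra enrolment is needed.
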